# RESEARCH CHECKLIST for “A prospective study on an innovative online forum for peer reviewing of surgical science”

[name], [name], [name], [name], [name], [name]

1. Study protocol. The complete study protocol is found below.
2. This trial did not involve any patients, and is probably best described as an observational study. Therefore, the STROBE guidelines were followed when designing and reporting the study. The manuscript has been checked against the STROBE checklist and all items are covered. The STROBE checklist is included in this research checklist, please see below.

## Background

Peer review is important for authors, editors and the whole scientific community. A survey of over 4000 international authors revealed that whilst 91% believe that peer review has improved their work, 2/3 feel that conventional peer review can be improved.^1, 2^ Current peer review models can induce bias ^3-11^, fail to identify error and fraud ^12-15^ and suppress innovation.^16^ Thus, new and innovative models of peer review are needed. Therefore, we propose an open peer review system where a wider audience is invited to review papers online. Due to uncertainty about the acceptance of such a novel peer review process, a feasibility study will be performed at first, where authors are invited consecutively to subject their submitted papers to online open review in addition to standard peer review.

## Aim

- To explore whether authors, editors and reviewers are prepared to participate in a peer review process via an online open peer review system, in order to prepare for a larger randomised controlled trial
- To explore the acceptability of this process to authors, reviewers and editors
- To evaluate the advantages, disadvantages and practical issues associated with such a process

## Hypotheses

**Null hypothesis**

- The open peer review process is as feasible in terms of reviewers’ and editors’ engagement and results in referee reports of equally good quality.

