**Alternative hypothesis**

- The open peer review is not feasible, because participation rates are too low and/or there is too little perceived benefit by authors, reviewers and/or editors

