**Outcome assessment**

- **Main outcome**
  - Quality of referee reports (based on the used review quality instrument)
- **Secondary outcomes:**
  - Participation rate, i.e. number of reviews and/or author comments per paper in open peer review
  - **Quality of referee reports (based on the BJS scoring system for peer review quality)**
  - **Reviewer’s recommendation regarding publication (**accept paper without changes needed, publish with major revision, publish with minor revision, reject.)

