**Study time frame**

Consecutive papers are included within a predefined timeframe.

- - Start date: 1^st^ April 2015
  - End date: 31^st^ May 2015

This will yield approximately 170 papers (taking into account that roughly 150 papers are submitted to BJS each month, that roughly n=25 papers per month are rejected outright without undergoing formal peer review and that roughly 70% of authors will provide informed consent for the study).

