**Data management and analysis**

The quality of the referee reports between the two different review processes (standard *versus* open) will be compared using non-parametric statistics.

Number of open reviews per paper and number of comments per paper will be calculated.

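### Equal quality is stated as the null and tested only for a difference, so the plan cannot show equal quality, and a quality deficit with good participation fits neither hypothesis

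*Combined protocol and SAP*

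**What the plan says.** The Null hypothesis has two parts. On feasibility it begins "The open peer review process is as feasible in terms of" and names reviewers' and editors' engagement. On quality it adds that open review "results in referee reports of equally good quality".

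The Alternative hypothesis reads "The open peer review is not feasible, because participation rates are too low and/or there is too little perceived benefit" by authors, reviewers or editors. It gives no cut-off and does not mention report quality.

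Outcome assessment makes the review quality instrument score the main outcome and participation a secondary one. It lists no measure of perceived benefit.

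Data management and analysis gives the whole comparative plan in one sentence: quality under the two processes "will be compared using non-parametric statistics". For participation, "Number of open reviews per paper and number of comments per paper will be calculated". No significance level, named test, margin, confidence interval or decision rule is given. The roughly 170 papers under Study time frame are an accrual forecast, not a power calculation.

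**The concern.** A difference test starts from equality and asks whether the data contradict it. When equality is also the conclusion the investigators hope for, a small or noisy data set leaves that conclusion standing without having supported it. The plan contains nothing that separates a well-estimated difference near zero from too few reports to tell.

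The number of open reports is itself uncertain; finding it out is one reason for the study. If open reports are truly worse, the quality test is least able to show it when few arrive.

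The two hypotheses also do not cover all outcomes. The main outcome's only comparison does not bear on the alternative, and the alternative's criterion has no number. Under Aim, the study is meant to prepare for a larger randomised trial, so its quality and feasibility findings should be readable without a judgement made after the data are seen.

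**Working it through.** **1. The plan's own figure.** Study time frame gives 150 submissions a month, 25 rejected outright, two months and 70% consent: (150 − 25) × 2 × 0.70 = 175, against about 170 stated. The forecast reproduces to within rounding. It says nothing about how many papers will have open reports.

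**2. Which hypothesis covers which result.**

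| Open-report quality | Participation | Hypothesis that fits |
| --- | --- | --- |
| Equal | Good | Null |
| Worse | Good | Neither |
| Equal | Low | Alternative, in words; no cut-off |
| Worse | Low | Alternative, on participation only; no cut-off |

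The second row is the gap. The last two depend on a value for low participation that the plan does not set.

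**3. How often a real deficit would be missed.** The documents give no SD, effect size, significance level or expected number of papers with both kinds of report. Assumed: two-sided 5% paired t-test on within-paper differences, SD of the difference 0.8 or 0.6, true deficit 0.4 or 0.25 points on the 1-to-5 scale, n paired papers. The noncentrality is √n × deficit / SD, and the miss probability is the noncentral t probability of falling between the critical values. For n = 20, deficit 0.4, SD 0.8: √20 × 0.4/0.8 = 2.236, critical value 2.093 on 19 df, miss probability 44%.

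| Paired papers | Deficit 0.4, SD 0.8 | Deficit 0.25, SD 0.8 |
| --- | --- | --- |
| 20 | 44% | 74% |
| 30 | 25% | 62% |
| 50 | 7% | 42% |
| 80 | 1% | 21% |
| 170 | about 0% | 2% |

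With SD 0.6 and 20 papers the figures are 19% (deficit 0.4) and 58% (deficit 0.25).

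**4. The same check with an unpaired rank test.** The standard process needs at least two reports per paper, so at least 2 × 170 = 340 standard reports. With m open reports, all reports treated as independent, a deficit of 0.5 SD and rank-sum efficiency 0.955, the expected test statistic is 0.5 / √[(1/340 + 1/m)/0.955], compared with 1.96. A non-significant result has probability 81% at m = 5, 44% at 20, 10% at 50 and 1% at 100. Simulation of the Mann-Whitney test agrees within about 3 points. With no true difference the probability is about 95% at every m, so the link with participation needs a true deficit.

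**5. Behaviour of a confidence-interval rule.** With 340 standard reports, an assumed margin of 0.5 SD, a normal approximation and no true difference, the chance that the 95% interval excludes the margin is 20% at 5 open reports, 34% at 10, 58% at 20 and 91% at 50. If open reports are truly worse by the margin, it is 2.5% throughout. Sparse data no longer favour the claim.

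In the paired setting with SD 0.8, 80% power and no true difference, a margin of 0.4 needs (0.8 × 2.80/0.4)² = 31.4, about 32 papers (normal approximation). A margin of 0.2 needs (0.8 × 2.80/0.2)² = 125.4, about 126. A margin of 0.2 with a true deficit of 0.1 leaves 0.1 to spare and needs (0.8 × 2.80/0.1)² = 501.8, about 502, more than the forecast.

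**The case against.** A reader might infer that the plan counts a non-significant test as success. The documents do not support that: no section gives a p-value rule or a rule for concluding equality. The wording invites the reading and nothing excludes it, which is a weaker statement.

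A reader might also infer that the fewer open reports arrive, the more surely the plan retains feasibility, or that feasibility could never be rejected. That goes too far. The null joins feasibility and quality, and the alternative names low participation as a ground for non-feasibility. Participation is also to be calculated. Near-zero participation would, in the plan's own words, point to non-feasibility. The perverse link is confined to the quality half and exists only if there is a true deficit. What stands is that, without a cut-off, the feasibility call is made after seeing the data, and no rule makes it override a non-significant quality result.

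The miss rates rest on assumed SDs, deficits and numbers of papers, and on a paired t-test where the plan specifies non-parametric methods and does not mention pairing. That is fair, although the rank-test check shows the same pattern. With paired reports on all 170 papers the problem nearly disappears for the deficits considered.

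Finally, this is an exploratory feasibility study. No stated rule ties the quality result to launching the later trial, and editorial decisions are made blind to the open reports. This lowers the severity. It does not remove the defect, because the protocol itself chose formal hypotheses and a comparative main outcome.

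**Conclusion.** The concern holds in limited form. The stated null and the single comparison cannot establish equal quality, the alternative leaves a quality deficit with good participation unclassified, and the feasibility criterion has no value. These are faults in the hypotheses as written, not merely missing detail.

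The size depends on how many papers attract open reports, for which the documents give no expectation. Under the SD 0.8 illustration, the chance of missing a real deficit ranges from substantial at 20 paired papers to negligible or small at 170. Clustering of reports within papers could change the exact probabilities in the rank-test check, but fewer open reports would still mean less power.

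This should be fixed before scoring. Given the exploratory purpose, it does not invalidate the study.

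**What to change.** Reword the two hypotheses and the analysis section so that equality is no longer the null.

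- **Quality.** Report the open-minus-standard difference in instrument score with its 95% confidence interval. Conclude equal quality only if the lower limit lies above minus a margin that the editors fix before scoring. Otherwise report the estimate and interval as inconclusive on equal quality.
- **Feasibility.** Judge it separately, never from the quality test. Compare participation per paper, with its confidence interval, with a threshold the editors set in advance.

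Both numbers are for the editors to choose. As illustrations only, the margin might be 0.4 points (10% of the 4-point range) and the participation criterion two open reports per paper. The latter borrows the minimum number of reports in the standard process, which nothing in the plan applies to open review. The paper counts in step 5 show how strongly the margin governs what is achievable.

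The cost is rewording three short sections and agreeing two numbers. The downside is that a study with few open reports can no longer claim equal quality.

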**Alternative hypothesis**

- The open peer review is not feasible, because participation rates are too low and/or there is too little perceived benefit by authors, reviewers and/or editors

## Methods/Design

**Setting**

This study will be performed by the assistant editors of BJS. BJS will act as sponsor of the trial.

**Study design**

An observational feasibility trial. Included papers will undergo conventional peer review and simultaneous open peer review.

**Eligibility assessment and consent**

Submitted manuscripts are subject to internal reviewing. All manuscripts that are not immediately rejected will be eligible for enrolment. Informed consent is asked for at the time of submission of the paper online via Scholar One. Inclusion into the study is only performed once an informed consent by the corresponding author is given using an electronic signature.

**Standard peer review process**

In the standard process, the manuscripts are subject to external reviewing only. The handling editor sends the paper to two to four referees of his/her choice. The referees are asked to return their reports to the editorial office within two weeks. Referees use the current online evaluation forms. After submission of at least two referee reports, the handling editor scores the reports according to standard BJS policy and according to the existing specific review quality instrument as described below.

Eventually, the handling editor makes a decision: accept paper without changes needed, invitation to resubmit the paper following major or minor revisions or rejection of the manuscript. This review process takes on average 22 days. By default, the open peer review is single-blinded in which the reviewer’s name is not disclosed to the authors.

**Open peer review through online system**

Following submission a manuscript will simultaneously go through standard peer review and also to the innovative process under study.

At the same time, the manuscript will be posted on a dedicated website for open access reviewing using Google Docs.

A mail is sent out every fortnight inviting potential referees as outlined below to review posted papers Abstracts of posted papers are included in this mail as well as a direct link to the paper and the online website. The email also contains an unsubscribe link.

Referees who like to review the paper on the open website are asked to adhere to the same online evaluation forms (standard referee sheet) as in the standard peer review process. It is also mentioned that the handling editor makes the final decision and that the reviewers should not mention in their reports whether the manuscript merits publication or not.

Once the review has been submitted, it will be immediately posted on the website and will be accessible to authors and other invited reviewers, i.e. open. By default, reviewers’ names and affiliations will be shown; anonymous reviewing is not allowed. Authors are notified via e-mail when a new review is posted.

After a period of 21 days, the manuscript and corresponding referee reports will be removed from the website and stored at manuscript central?).

**Final decision**

The responsible editor handles the manuscript in a standard way; he/she makes a decision, based on the standard peer review blinded to the comments from the open peer review process. Once the final decision is made, he/she then evaluates the online open referee reports according to standard BJS policy. The referee reports from the open review process are available to the author and can be used to improve the paper when resubmission is requested (first revision, i.e. R1) or for submission to another journal.

The assistant editors however, score all referee reports (invited reports and those from the open review process) according to the review quality instrument as described below. The assessors are not blinded to the source of the referee reports (invited *versus* open).

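### BJS quality score: standard reports are scored before the decision and open reports after it, so scoring time and order cannot be separated from review source

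*Combined protocol and SAP*

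**What the plan says.** The Outcome assessment section of the Combined protocol and SAP lists two measures of report quality. The main outcome uses the review quality instrument. A secondary outcome is quality "based on the BJS scoring system for peer review quality". The items of the BJS system are not described.

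For standard reports, the Standard peer review process section says: "After submission of at least two referee reports, the handling editor scores the reports according to standard BJS policy". The decision comes later in the same section: "Eventually, the handling editor makes a decision". On duration it says: "This review process takes on average 22 days".

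For open reports, the Final decision section first protects the decision: "he/she makes a decision, based on the standard peer review blinded to the comments from the open peer review process". It then continues: "Once the final decision is made, he/she then evaluates the online open referee reports according to standard BJS policy". The Open peer review through online system section sets a separate end to the posting: "After a period of 21 days, the manuscript and corresponding referee reports will be removed from the website".

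The Data management and analysis section compares report quality between standard and open review with non-parametric statistics. It does not say which of the two scores is meant. No section sets a common scoring time, a random scoring order, a rescoring step or an adjustment for timing.

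**The concern.** A comparison of two sets of reports is fair only if both are scored under the same conditions. Here the editor scores the standard reports while they are new and the decision is still open. The same editor meets the open reports only after reading the standard ones and committing to a decision. If timing or order has any effect on the score, all of it goes into the standard-versus-open difference.

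A second, smaller gap concerns completeness. Evaluation of the open reports is allowed from the decision onwards, while posting runs for a fixed 21 days. Nothing says that evaluation waits until posting has closed. If the decision comes early and the editor evaluates at once, reports posted later may have no BJS score.

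The score is secondary, but report quality is part of the null hypothesis in the Hypotheses section, and the Aim section presents the study as preparation for a larger randomised trial. That trial could inherit the same scoring schedule.

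**Working it through.** **1. The plan's own figure.** The Study time frame section gives about 150 submissions a month, about 25 rejected outright, about 70% consent, and two months. (150 − 25) × 0.70 × 2 = 175, which agrees with the stated figure of approximately 170. The point does not depend on this number; it is used only for scale.

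**2. The two schedules side by side.**

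| | Standard reports | Open reports |
| --- | --- | --- |
| BJS scorer | Handling editor | Responsible editor, taken to be the same person |
| Earliest time | When at least two reports are in | After the decision |
| Relative to the decision | Before | After |
| Relative to the other set | First | Second |

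That standard reports are scored before the decision is read from the order of the steps in the Standard peer review process section.

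**3. What can be estimated.** Let S = 1 for an open report and 0 for a standard one, and T = 1 if scored after the decision and 0 if before. Take score = a + bS + cT + error. As scheduled, T = S for every report, so score = a + (b + c)S + error. Only the sum b + c can be estimated. The correlation of S and T is 1.0, and the design matrix [intercept, S, T] has rank 2 of 3.

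If all reports are scored after the decision, T is constant. With a shuffled order O, the matrix [intercept, S, O] has rank 3 of 3, so session order can be separated from source. One variable stays aliased even then: whether the editor had already read the report and used it for the decision, which equals 1 − S.

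**4. What a shift would do (illustration only).** Assumptions not in the documents: no true difference, independent reports, a two-sided 5% test, one open report per paper, and a normal approximation. With shift d in SD units, SE = √(1/n₁ + 1/n₂) and P(significant) = Φ(d/SE − 1.96) + Φ(−d/SE − 1.96).

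| Shift d | 170 standard, 170 open | 340 standard, 170 open |
| --- | --- | --- |
| 0 | 0.05 | 0.05 |
| 0.1 | 0.15 | 0.19 |
| 0.2 | 0.45 | 0.57 |
| 0.3 | 0.79 | 0.89 |
| 0.5 | 1.00 | 1.00 |

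For d = 0.2 and 170 per set: SE = √(2/170) = 0.108, d/SE = 1.84, Φ(−0.12) = 0.45. The table shows sensitivity to a shift. It is no evidence that one exists.

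**5. Decision against end of posting.** The documents give a mean of 22 days and a posting of 21 days, but no spread. Assume that both clocks start together and that the time to decision is normal with SD 5 to 10 days. Then P(decision before day 21) = Φ((21 − 22)/SD), which is Φ(−0.2) = 0.42 to Φ(−0.1) = 0.46, or 72 to 78 of 170 papers. A lognormal with the same mean and SDs gives about 46% to 54%. These are papers decided before posting closes. The number of reports left unscored does not follow from them.

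**The case against.** The strongest defence is that the order is deliberate: it keeps real editorial decisions free of the open comments. That stands, and the fix leaves it untouched. It is also true that this is one secondary outcome in a feasibility study. That limits the weight of the point but does not remove it.

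Four further objections narrow it.

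- A reader might infer that open reports will be marked down, because repeated points look redundant and dissent looks wrong in hindsight. The documents do not support a direction. The BJS items are not described, and open reviewers are told not to say whether the paper merits publication, which weakens the dissent argument.
- A reader might infer that nearly half the papers lose open reports. The text does not say so. The Final decision section sets an earliest time for evaluation and no cut-off, and reports are to be stored after removal from the website. The 42% to 46% rests on an assumed spread and a common start. If the decision meant is the one after revision, most of this risk disappears.
- A late third or fourth standard report could be scored after the decision. The plan makes no provision for this, and it would still place no open report before the decision.
- A common session cannot undo the editor's earlier use of the standard reports, and source remains visible. This is correct, and is why the fix also changes how the result is reported.

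**Conclusion.** The point holds for the BJS score. On the schedule as written, source is completely aliased with scoring time and order, and the planned comparison cannot separate them. This rests on reading the steps in the Standard peer review process section as sequential, on the same editor scoring both sets, and on the planned quality comparison including the BJS score. Size and direction of any bias are unknown. Open reports posted after an early decision are at risk of going unscored, in unknown number.

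A reader might extend this to the main outcome. The documents do not support that: the assistant editors score all reports with the review quality instrument, and no before-and-after split is stated for them. The Standard peer review process section also has the handling editor apply that instrument to standard reports, so the plan should say whose instrument scores are analysed. The change should be made, but it does not threaten the study's main result.

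**What to change.** Keep the decision blinded to the open reports. Then amend the Standard peer review process and Final decision sections as follows.

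- The study's BJS score for all standard and open reports of a paper is given by the handling editor in one session, in shuffled order, after the later of the first decision and day 21.
- Where editorial practice allows, the BJS score of standard reports is deferred to that session. Otherwise the earlier score is for routine use only and is not the study outcome.
- The decision meant is the first decision, so that scoring does not wait for revision rounds.
- The stored open reports are available to the editor for that session. The place of storage is still marked with a query in the section on the online system.

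In the Data management and analysis section, label the BJS comparison descriptive. State that the editor had already read and used the standard reports and was not masked to source.

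The cost is a few sentences and later scoring. If the standard-report score cannot be deferred, some scoring is repeated by the same editors. At two to four referees per paper, that is at most 170 × 2 = 340 to 170 × 4 = 680 standard reports, if every invited referee reports. Deferral avoids the repetition.

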**Review quality instrument version 4**

An established validated review quality instrument consisting of seven items formulated as questions that relate to importance of the research question, originality, method, presentation, constructiveness of the comments, substantiation of comments and interpretation of results is used. Each of the seven items scores in a five-point Likert scale from 1 (=poor) to 5 (=excellent). An additional eighth question assessed the overall tone of the review ranging from abusive to courteous. A total score is based on the mean of the eight items scores.17 (Figure 1)

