## Timeline

- Discussion with BJS digital manager regarding website.
- Approval of protocol at BJS meeting in March 2015 (Birmingham) – done!
- Testing of the website during March: a pilot study with 10 papers will be necessary, for which the open peer review process will be simulated by the assistant editors only without involving external referees.
- Timely start of the trial April 1^st^ 2015
- Presentation of preliminary results at BJS meeting in May 2015 (Maastricht)
- Report of study results at BJS meeting in July (London).
- Publication is expected to be finalised in autumn 2015.

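### The plan does not say how reports are allocated to the several editors who score the main outcome, or whether the comparison is paired by paper, so differences in rater leniency may enter the standard-versus-open difference.

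*Combined protocol and SAP*

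**What the plan says.** The main outcome (Outcome assessment) is "Quality of referee reports (based on the used review quality instrument"). Under Review quality instrument version 4, each item is graded from 1 to 5, and "A total score is based on the mean of the eight items scores".

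Two sections say who gives this score.

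- **Final decision:** "The assistant editors however, score all referee reports (invited reports and those from the open review process"). The same section adds that "The assessors are not blinded to the source of the referee reports".
- **Standard peer review process:** once at least two reports are in, "the handling editor scores the reports according to standard BJS policy and according to the existing specific review quality instrument as described below". For the open reports, Final decision has the handling editor apply only the journal's usual policy and does not mention the instrument.

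Under Study design, each included paper goes through both processes. Under Data management and analysis, report quality in the two processes "will be compared using non-parametric statistics". The plan does not give the number of assistant editors, the allocation of reports to them, any duplicate scoring or averaging, or a pairing of the comparison by paper.

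**The concern.** Editors differ in how generously they grade. Because each paper is meant to receive both kinds of review, an editor's general leniency can be removed from the contrast: the same editor scores both kinds for a paper, and the difference is taken within the paper. The plan has the structure for this but does not commit to using it.

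The workload makes the question practical. About 170 papers with at least two standard reports each give at least 340 standard reports, plus the open ones. Sharing the work among editors is therefore plausible, and the way it is shared decides whether leniency cancels, adds noise or biases the main outcome.

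**Working it through.** **The plan's own figure.** Study time frame gives 150 submissions a month, 25 immediate rejections a month, 70% consent and two months. (150 − 25) × 2 × 0.70 = 175, in line with the stated figure of about 170. The plan states no SD, effect size, alpha or power, so there is no precision figure to reproduce.

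**Inputs.** From the plan: two standard reports per paper, the minimum under Standard peer review process. Assumed, because the plan gives none of these: one open report per paper, report-level SD s = 0.7, rater leniency SD r = 0.4 to 0.6, K = 4 raters, no true difference, and 85 papers with an open report (half of 170). The percentage changes in SE do not depend on the number of papers.

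**Contrast.** D = mean of the two standard scores minus the open score, within a paper.

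1. *One rater per paper, paired analysis.* An additive leniency term cancels. Var(D) = s²(1/2 + 1) = 0.49 × 1.5 = 0.735, so SD = 0.857. SE = 0.857/√85 = 0.093 (0.066 with 170 papers). The simulated false-positive rate of a paired Wilcoxon test is about 5%.

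2. *Reports divided at random, without regard to source.* With a pool of K raters, Var(D) = 1.5 × [s² + r²(1 − 1/K)].
   - r = 0.4: 1.5 × (0.49 + 0.12) = 0.915; SE = √(0.915/85) = 0.104; ratio √(0.915/0.735) = 1.12.
   - r = 0.6: 1.5 × (0.49 + 0.27) = 1.140; SE = √(1.140/85) = 0.116; ratio √(1.140/0.735) = 1.25.
   - Simulation agrees (SE 0.102 to 0.104 and 0.113 to 0.118), and the false-positive rate stays near 5%. This is noise, not bias.

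3. *Every editor scores every report, scores averaged.* Each report carries the same average leniency, so it cancels.

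4. *Different raters for the two sources (illustrative worst case).* With two of four raters on each source, leniency becomes a shift with SD r√(4/K) = r. For r = 0.2, 0.4 and 0.6 and 85 papers, simulated false-positive rates are about 40%, 60 to 65% and 70 to 73%. The mean absolute spurious difference is about 0.18, 0.33 and 0.49 points.

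**Could case 4 arise under this plan?** The standard reports may end up with two sets of instrument scores, one from the handling editor and one from the assistant editors. The open reports have instrument scores from the assistant editors only. The plan does not say which set is analysed. If handling-editor scores were used for standard reports and assistant-editor scores for open ones, rater and source would be confounded.

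**The case against.** A reader might infer that the plan biases its main result. The documents do not support that. Final decision gives reports from both sources to one group in one task, and no section describes a split by source. Its wording can even be read as every assistant editor scoring every report, in which case leniency cancels. A large workload suggests that scoring is shared, not that it is shared by source. Under source-neutral sharing the test keeps its nominal error rate, so an editor who happens to score more open reports adds chance variation that the test already allows for.

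Other fair points: non-parametric statistics can include a paired test, so the plan is silent on pairing and does not rule it out. Same-rater pairing helps only papers that attract an open review, and participation is itself an outcome. One unblinded rater who sees both kinds of report together may be open to contrast or preference effects. The study is a feasibility trial with no stated power, so a modest loss of precision is not critical.

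All of this stands, and it limits the point to an unstated allocation with a possible effect. It does not remove the point, because the reading that is harmless and the one that is not are equally compatible with the text, and the two sections on who scores the standard reports still need to be reconciled.

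**Conclusion.** The point holds in conditional form. The plan leaves rater allocation and pairing open, so it does not ensure that leniency cancels in the main comparison. The likely cost, if reports are shared without regard to source, is a standard error about 10 to 25% larger than necessary. That range rests on the assumed residual SD of 0.7, rater SD of 0.4 to 0.6, four raters, and two standard and one open report per paper. Bias needs raters who differ by source; the unresolved roles of handling and assistant editors are the one route to this that the text itself contains. The high false-positive rates in case 4 show what that route could do and are not a forecast. This is a worthwhile and cheap improvement, not a fatal flaw.

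**What to change.** - **Source of the score.** State that the main outcome uses assistant-editor scores only, and reconcile Standard peer review process with Final decision on who applies the instrument to the standard reports.
- **Allocation.** Have the same assistant editor, or the same fixed pair, score all reports of a paper, standard and open, in random order after its open window has closed. Record the rater.
- **Analysis.** Make the main comparison the within-paper difference among papers with at least one open report, for example a Wilcoxon signed-rank test on paper-level means. Report how many papers this excludes.
- **Alternative.** If every assistant editor is to score every report, say so, and average over editors before the paired test.

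The cost is an allocation list, one recorded field and a sentence of analysis text, with no extra staff. Two downsides remain. Scoring of the standard reports waits for the 21-day window, so a paper posted on the last enrolment day, 31 May, could not be scored before 21 June. An unblinded rater also sees both sources side by side. The change removes differences in general leniency between raters; it does not remove any preference a rater has for one process, so the lack of blinding needs separate treatment.
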